## 2 AIMS AND OBJECTIVES

### 2.1 Main Trial Objectives

#### 2.1.1 Clinical Aims and Objectives

To evaluate whether in children undergoing cardiac surgery with cardioplegic arrest, the use of del Nido cardioplegia, compared with St. Thomas' blood cardioplegia:

- reduces myocardial injury, as determined by AUC for plasma troponin following surgery
- reduces the duration of ischaemia (aortic cross-clamp time), the volume of cardioplegia given, and the need for internal defibrillation during reperfusion
- improves myocardial protection, reducing the frequency or severity of LCOS, and markers of reduced tissue perfusion (arterial lactate and *omega*)
- improves other clinical outcomes, including duration of mechanical ventilation, length of stay on the Paediatric Intensive Care Unit and in hospital, and 30-day survival

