## 6 ENROLMENT AND RANDOMISATION

### 6.1 Enrolment and Screening

Patient eligibility will be confirmed by a member of the research team who is medically qualified, i.e. by a doctor. All baseline assessments will be carried out after informed consent and prior to patient randomisation.

At baseline, prior to randomisation, the following assessments will be performed:

- Patient demographics
- Preoperative weight and height/length
- Resting oxygen saturations
- Preoperative haematocrit
- Comorbidities
- Preoperative medications

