## 7 TRIAL TREATMENT / INTERVENTION

### 7.1 Intervention(s) and Schedule

The trial interventions are either del Nido cardioplegia (experimental arm) or St. Thomas' blood cardioplegia (control arm). The two cardioplegia solutions are compared in **Table 1**.

| del Nido cardioplegia                                                 | St. Thomas' blood cardioplegia (Harefield preparation) |
|-----------------------------------------------------------------------|--------------------------------------------------------|
| 1 litre Plasma-Lyte A base solution to which the following are added: |                                                        |
| Mannitol 20%, 16.3ml                                                  | Sodium chloride 8.6g                                   |
| Magnesium sulfate 50%, 4ml                                            | Magnesium chloride 6.262g                              |
| Sodium bicarbonate 8.4%, 13ml                                         | Calcium chloride 330mg                                 |
| Potassium chloride 2mEq/ml, 13ml                                      | Potassium chloride 6.252g                              |
| Lidocaine 1%, 13ml                                                    | Procaine hydrochloride 1364mg                          |
| Total volume: 1052.8ml                                                | In water for injection, per 1000ml                     |

**Table 1.** Table comparing the crystalloid components of the experimental (del Nido) and control (St. Thomas') treatments [42].

The del Nido and St. Thomas' blood cardioplegia also differ in their formulations and doses as depicted in **Table 2**.

| Arm          | IMPs                          | Formulations                                               | Dose                                                                                                           |
|--------------|-------------------------------|------------------------------------------------------------|----------------------------------------------------------------------------------------------------------------|
| Experimental | del Nido cardioplegia         | 1:4 blood:crystalloid preparation                          | Initial dose of 20ml/kg and subsequent doses every 60-90 minutes if required, at the discretion of the surgeon |

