| Control      | St Thomas' blood cardioplegia | 4:1 blood:crystalloid using Harefield Hospital preparation | Initial dose of 20-30ml/kg, subsequent doses of 15 ml/kg every 20-30 minutes, at the discretion of the surgeon |

**Table 2.** Acceptable formulations of IMP and dosage of experimental vs control arm.

The allocated cardioplegia solution will be administered according to the above preparation and schedule by the Clinical Perfusionist, at the request of the operating surgeon, in an antegrade manner via an aortic root or direct coronary ostia canula, following placement of a cross-clamp on the proximal aorta. The glass bottle containing the IMP should be vented using a spike vent or similar during infusion. By placing a waste sucker into the right atrium after commencing its delivery, the systemic bioavailability of the cardioplegia constituents following passage through the coronary circulation will be markedly reduced.

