### 8.2 Secondary Outcome Measures

- Low cardiac output syndrome (LCOS) defined as either of the following in the first 48 hours after reperfusion: Vasoactive Inotrope Score (VIS)  $\geq 15$  [1,2], or major cardiac event (cardiac arrest, ECLS or death) (n) [3]
- Duration of mechanical ventilation (hours), defined as the number of hours from termination of index CPB to extubation
- Length of postoperative stay on Paediatric Intensive Care (hours), defined as number of hours from admission to PICU from theatre following index procedure to discharge from PICU
- Maximum VIS by thresholds:  $\geq 10$ ,  $\geq 15$  and  $\geq 20$  in the first 48 hours (n)
- Total VIS in the first 4 hours after PICU admission following the index procedure (score)
- Arterial lactate (mmol/L) in the first 12 hours
- *Omega*, determined by  $[\text{SaO}_2]/[\text{SaO}_2 - \text{ScvO}_2]$  in the first 12 hours [4]
- Total aortic cross-clamp time (mins)
- Total volume of cardioplegia given (ml)
- Need for internal defibrillation during reperfusion (n)
- Delayed sternal closure, incidence (n) and duration (days)
- Unplanned reoperation, including chest re-opening on PICU (n)
- Need for new renal replacement therapy (n)
- Lowest estimated glomerular filtration rate (eGFR), calculated using the bedside Schwartz equation and the peak postoperative creatinine on routine monitoring during the first 7 days following the index procedure ( $\text{ml/min/1.73m}^2$ ), and according to the paediatric RIFLE categories (n) [5]
- Length of postoperative stay in the hospital (days), defined as number of days from day of surgery to discharge from hospital or death, whichever is sooner
- 30-day survival (n)

Detailed information on postoperative healthcare resource use will be collected on all patients from the Paediatric Critical Care Minimum Data Set (PCCMDS) [43], via the Paediatric Intensive Care Audit Network (PICANet), to which all centres routinely contribute. This dataset will be compared with data collected on the trial CRFs to assess the feasibility of using routinely collected outcome data in a trial setting and to inform planning of cost-effectiveness analyses in future trials.

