### 13.2.2 Secondary Outcome Measures

Continuous data items will be analysed using a linear regression model. Results will be presented as adjusted mean difference and 95% confidence intervals.

Continuous outcomes measured across more than 3 time points (e.g. arterial lactate and omega) will be analysed as repeated measures using linear mixed models using all available data. Baseline value of the measure (if available) and time by treatment interaction will be included with time as a continuous variable. Results will be presented as mean difference and 95% confidence intervals.

Time-to-event data outcomes (such as time from admission to PICU to discharge from PICU) will be analysed using the Cox regression model. Results will be presented as Hazard ratio and 95% confidence intervals. Kaplan Meier plots will also be presented with the log-rank test for visual interpretation.

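### Total cardioplegia volume is analysed in ml although dosing is per kg, so the mean difference is weighted towards heavy children and shifts with case mix; ml/kg is the better scale, at no cost (minor)

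*Protocol*

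**What the plan says.** Protocol 8.2 lists "Total volume of cardioplegia given (ml" among the secondary outcomes, and the Trial Summary gives the same unit. The outcome serves a named aim in 2.1.1: to find out whether del Nido "reduces the duration of ischaemia (aortic cross-clamp time), the volume of cardioplegia given, and the need for internal defibrillation during reperfusion".

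Table 2 in 7.1 gives the dosing. The experimental arm is "Initial dose of 20ml/kg and subsequent doses every 60-90 minutes if required, at the discretion of the surgeon", with no volume stated for a repeat dose. The control arm is "Initial dose of 20-30ml/kg, subsequent doses of 15 ml/kg every 20-30 minutes, at the discretion of the surgeon". Section 4 admits children under 16 years and excludes those above 50 kg.

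For the analysis, 13.2.2 states: "Continuous data items will be analysed using a linear regression model". Section 13.2 adjusts for the minimisation variables of 6.2.1 where possible. These are four age bands (neonate, infant, 1 to under 7 years, 7 to under 16 years), anticipated ventricular incision or resection, and centre. Weight is not among them, although 6.1 lists "Preoperative weight and height/length" as a baseline assessment before randomisation.

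**The concern.** Total volume is body weight multiplied by the volume given per kg. The solution and its re-dosing interval act on the second factor. The first is fixed before randomisation and varies widely in this population, including within an age band. A mean difference in ml therefore combines the effect on dosing with the weights of the children who happened to be recruited.

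Three things follow. The estimate leans on the heaviest children. It would differ in a centre with another age mix even if surgeons dosed identically per kg. It also carries weight-related noise that age-band adjustment removes only in part. Elsewhere the protocol already scales size-dependent measures: the inotrope score uses doses per kg and eGFR is per 1.73 m². What is at stake is the readability and precision of one secondary estimate tied to a named objective, not the primary result or safety.

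**Working it through.** The protocol states no expected volume or effect for this outcome, so there is no figure of its own to reproduce.

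**1. From the protocol's doses alone.** One dose of 20 ml/kg is 20 × 50 = 1,000 ml at the 50 kg limit and 20 × 3 = 60 ml at 3 kg (an assumed newborn weight), a 17-fold spread from weight. Take an operation with two control repeats and a single del Nido dose:

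- control: 20 + 2 × 15 = 50 to 30 + 2 × 15 = 60 ml/kg
- del Nido: 20 ml/kg
- difference: 30 to 40 ml/kg at any weight
- the same difference in ml: 90 to 120 ml at 3 kg, 1,500 to 2,000 ml at 50 kg

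**2. Simulation.** From the protocol: 220 children, taken as 110 per arm; the per-kg doses and intervals above; the 50 kg cap; adjustment for age band. Assumed, because the protocol gives no values: median weights of 3.3, 6, 13 and 30 kg in the four bands, median cross-clamp time of 70 minutes, three age mixes, and 10 ml/kg for a repeat del Nido dose. That last figure is a modelling value only, not a suggestion about dosing. Each mix used 1,500 simulated trials, balanced within age band. Centre and ventricular incision were not modelled. The information ratio is (mean |t| in ml/kg ÷ mean |t| in age-adjusted ml)², calculated before rounding.

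| Age mix, youngest to oldest (%) | Difference, ml (age-adjusted) | Difference, ml/kg | Mean absolute t, ml | Mean absolute t, ml/kg | Information ratio |
|---|---|---|---|---|---|
| 25 / 40 / 25 / 10 | -408 | -41.6 | 9.8 | 18.6 | 3.6 |
| 15 / 40 / 30 / 15 | -487 | -41.6 | 10.1 | 18.6 | 3.4 |
| 10 / 30 / 35 / 25 | -612 | -41.5 | 10.4 | 18.5 | 3.2 |

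**3. Why the ml figure moves.** It is in effect the per-kg difference times the mean weight of the sample: 408/41.6 = 9.8 kg, 487/41.6 = 11.7 kg and 612/41.5 = 14.7 kg. Dosing behaviour is the same in all three rows.

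**4. Who supplies the ml difference.** In the middle mix, using median weights, older children contribute about 0.15 × 30 × 41.6 = 187 of 487 ml, or 38% (about 40% in the simulation, where the mean weight exceeds the median). Neonates are an equal share of the sample and contribute 0.15 × 3.3 × 41.6 = 21 of 487 ml, or about 4%.

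**5. Alternatives.** Adding weight as a linear covariate to the ml model raises information only about 1.3-fold, because the treatment effect in ml itself grows with weight. Log(ml) adjusted for age band gives 3.4 to 4.2 times, similar to ml/kg.

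**6. Wider assumptions.** A further run under varied assumptions gave about -380 to -715 ml against -35 to -41 ml/kg, with information ratios of roughly 2.1 to 3.6.

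**The case against.** Much of the case for leaving ml alone stands.

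- A reader might infer that the result mostly measures weight, or is confounded by it. The documents do not support that. Weight explains most of the spread between children in ml, but allocation is randomised 1:1, minimised on age and adjusted for age band, so the comparison is not biased.
- A reader might infer that the trial could miss a difference. In a similar simulation all 1,500 trials were significant in ml, with a largest p-value of about 5e-12. The arms' schedules largely determine that a difference exists.
- A reader might infer that unequal variance invalidates the ml regression. In that simulation the model standard error was 56.3 against an empirical 57.8, and 95% interval coverage was 94.1%. The ml/kg scale also has unequal variance between arms (SD about 22 ml/kg in control and 6 in del Nido), so this is no argument for either scale.
- Absolute ml answers a legitimate question about consumption. The product comes in 500 ml bottles, and the amendment log says the 50 kg limit was added to restrict use of several bottles for one child.
- The steady per-kg difference is partly built in, because the simulation doses exactly per kg. Table 2 leaves dosing to the surgeon's discretion, so the real contrast may vary with weight.

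It can also be said that scale and transformation belong in the SAP, which 13.2 promises and which is not at hand. This stands only in part. The SAP may add a per-kg analysis, but the unit of the outcome is fixed in the protocol itself, in two places, and the two documents should agree.

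**Conclusion.** The point holds as a minor, free improvement. The protocol's own doses show that a fixed per-kg contrast becomes about 17 times larger in ml at 50 kg than at 3 kg, so a single mean ml difference is dominated by heavier children and depends on case mix. This part needs only a newborn weight and a dosing pattern for illustration. The precision gain, about 2 to 3.6 times the information of age-adjusted ml, rests on assumed weights, age mixes, cross-clamp times and del Nido re-dose volume, and should be read as a range rather than a single figure. It would not change whether a difference is found. What improves is the estimate: tighter, and usable by a reader whose patients differ in size. The primary outcome and the safety analysis are untouched.

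**What to change.** In the Trial Summary, in 8.2 and in the SAP, define the analysed outcome as total cardioplegia volume per kg of preoperative weight (ml/kg). Keep total ml as a descriptive summary by arm and age band, which preserves the consumption figure. If the team prefers to stay with volume, log(ml) adjusted for age band performs similarly and gives a ratio of volumes. Whichever is chosen should be fixed before the outcome data are analysed, so that the scale is not a post-hoc choice.

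The cost is a change of unit in two places in the protocol and one in the SAP. Weight is already recorded before randomisation, so no new data are needed, and no dose, interval or other clinical rule changes.

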### 8.3 Study procedures

*Blood samples for troponin analysis:* Blood will be drawn from the indwelling arterial or central venous line at each of the predetermined timepoints: baseline (after induction of anaesthesia but prior to sternotomy) and at 3 hours, 6 hours, 9 hours, 12 hours, and 24 hours after reperfusion. If there is more than one period of aortic cross-clamping during the index operation, times should be calculated from the first cross-clamp removal. Each sample will be approximately 2ml, so in total approximately 12ml will be taken for troponin analysis. Plasma samples will be collected in EDTA tubes, spun, and split into two aliquots of at least 400 microl; if samples are taken overnight, they may be stored in a specified location in a PICU refrigerator and processed the following morning. Aliquots will be stored in a remotely monitored freezer at -80°C at the local site until transfer to Birmingham City Hospital, Birmingham or Midland Metropolitan University Hospital, Smethwick, for analysis of hs-troponin-I (Abbott, Abbott Park, IL). Samples will be analysed in batches approx. every 6 months so that data on the primary outcome is available to the DMC prior to each scheduled meeting. Additional details will be provided in the [DESTINY Troponin samples SOP](#).

*Blood gas samples:* Arterial lactate and arterial/central venous oxygen saturations (for calculation of *omega*) will be obtained from analysis of routine blood gas samples obtained at baseline (after induction of anaesthesia but prior to sternotomy) and at 3 hours, 6 hours, 9 hours, and 12 hours after reperfusion. If there is more than one period of aortic cross-clamping during the index operation, the times should be calculated from the first cross-clamp removal.

*Blood sample for genetic analysis:* With specific consent, 6ml of blood will be drawn from the indwelling arterial line at baseline into an EDTA tube and transferred to the local site laboratory. The buffy coat will be isolated, decanted into a standard 1.5ml Eppendorf tube, or similar, and stored in a remotely monitored freezer at -80°C until transfer in batches to the University of Birmingham where DNA extraction will be performed. Further details will be provided to each site in the [DESTINY Genetic samples SOP](#). At present, the extracted DNA will remain stored at -80°C and if additional funding is secured, genomic analysis will be performed.

*Biopsy samples for metabolic analysis:* At sites with liquid nitrogen available and with specific consent, myocardial tissue will be obtained from the right atrium during its routine incision at the onset of ischaemia and again at the end of ischaemia, in all patients. In patients undergoing routine resection of ventricular myocardium, such as hypertrophic septoparietal trabeculae from the right ventricular outflow tract or right ventricular free wall for anastomosis of an RV-PA conduit, these samples will be obtained during ischaemia when routinely resected. Specimens will each be washed in ice cold normal saline, placed in a cryotube (supplied), promptly snap-frozen in liquid nitrogen and stored in a remotely monitored freezer at -80°C at the local site until transfer for analysis at the University of Liverpool. Additional details will be provided to each site in the [DESTINY Biopsy samples SOP](#).

*Sample retention at the end of the trial:* It is expected that the process of analysis will result in the destruction of all blood and tissue samples analysed. At the end of the trial, application(s) may be made for any remaining samples, that have not been analysed within the scope of the main trial or sub-studies, to be used in future ethically approved research. Otherwise, all remaining samples will be either destroyed or transferred to the Human Biomaterials Resource Centre at the University of Birmingham.

## 8.4 Schedule of Assessments

**Table 3** below shows data collected at defined time points during the trial.

|                                          | Pre-operative | Pre-sternotomy | Intraoperative  |                  |                | Before leaving theatre | On PICU admission | Time since aortic cross-clamp removal (hours) |   |   |    |    |    | Daily until discharge | Hospital discharge |
|------------------------------------------|---------------|----------------|-----------------|------------------|----------------|------------------------|-------------------|-----------------------------------------------|---|---|----|----|----|-----------------------|--------------------|
|                                          |               |                | Onset ischaemia | During ischaemia | Late ischaemia |                        |                   | 3                                             | 6 | 9 | 12 | 24 | 48 |                       |                    |
| Screening                                | x             |                |                 |                  |                |                        |                   |                                               |   |   |    |    |    |                       |                    |
| Consent                                  | x             |                |                 |                  |                |                        |                   |                                               |   |   |    |    |    |                       |                    |
| Randomisation                            | x             |                |                 |                  |                |                        |                   |                                               |   |   |    |    |    |                       |                    |
| Clinical baseline data       | x             |                |                 |                  |                |                        |                   |                                               |   |   |    |    |    |                       |                    |
| Blood for hs-troponin-I                  |               | x              |                 |                  |                |                        |                   | x                                             | x | x | x  | x  |    |                       |                    |
| Arterial and central venous blood gases  |               | x              |                 |                  |                |                        |                   | x                                             | x | x | x  |    |    |                       |                    |
| Administer IMP or control cardioplegia   |               |                | x               |                  |                |                        |                   |                                               |   |   |    |    |    |                       |                    |
| Intraoperative biopsies      |               |                | x               | x                | x              |                        |                   |                                               |   |   |    |    |    |                       |                    |
| Conceal perfusion chart                  |               |                |                 |                  |                | x                      |                   |                                               |   |   |    |    |    |                       |                    |
| Inotrope data                            |               |                |                 |                  |                |                        | x                 | x                                             | x | x | x  | x  | x  |                       |                    |
| Other clinical outcome data  |               |                |                 |                  |                |                        | x                 |                                               |   |   | x  | x  | x  | x                     | x                  |
| SAE reporting if required                |               |                |                 |                  |                |                        |                   |                                               |   |   |    | x  | x  | x                     | x                  |

**Table 3.** Schedule of assessments.

 As collected in the Baseline CRF and described in section 8.2

 Right atrial +/- right ventricular biopsies at centres with liquid nitrogen available, as per section 8.3.

 As collected in the Postoperative CRF

